### Statistical Analyses

For the psychometric outcome analyses, all patients who were randomly assigned to the 2 conditions and completed the initial survey (T1) will be included in an intention-to-treat (ITT) analysis. All available data will be used for this purpose. Missing values in the data will be replaced by multiple imputations (multivariate imputation by chained equations with n=5 imputations) based on the control arm, using the variables “age” and “gender” as predictors in addition to the measurement-repeated stress indicators. In addition, last-observation-carried-forward, baseline-observation-carried- forward, reference-based-multiple imputation (jump-to-reference approach [49]), and completer sensitivity analyses will be performed.

The confirmatory analysis of the primary outcomes consists of calculating a mixed model with 2 measurement time points and a general correlation structure [47]. A random effect for the subjects is calculated (random intercept) and 3 fixed effects (group assignment, time, and the interaction of the 2 predictors). The 2 measurement time points are nested within subjects. The primary outcomes will be evaluated using a Bonferroni-Holm correction for α error inflation. Secondary confirmatory outcomes will only be analyzed if the results of the primary analysis confirm the hypotheses, and the same mixed model with a random intercept for the subject will be applied. Again, a Bonferroni-Holm correction will be used.

Independent 2-tailed *t* tests and chi-squared tests will be used to estimate differences between groups in pretreatment sample characteristics. In addition to the ITT sample, a “per-protocol” sample sensitivity analysis is defined for exploratory analyses, including all patients in the intervention group who completed at least 4 of the modules.

There are different approaches to calculating effect sizes for mixed modeling data in the literature [50]. Hedges [50] and Westfall et al [51] propose an effect size based on the Cohen *d*, which is also used for power analysis [47]:

To assess the magnitude of the treatment effects, the fixed interaction effect of time and group assignment is divided by the root of the summed variances of the random effects. Effect sizes can be roughly interpreted according to the Cohen *d*: effect sizes of 0.2 are considered small, 0.5 moderate, and 0.8 large [52]. Differences in response rates and additional health care service utilization rates are examined with 2-tailed *t* tests and chi-squared tests.

All data analyses are performed without knowing group membership (blinded data analysis). The evaluator does not know which expression of the group variable indicates membership in the intervention group and which indicates membership in the control group. Multimedia Appendix 1 shows example code for the R analysis of the outcomes.

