While most of the literature focuses on guided forms of iCBT with therapeutic support, minimally guided, self-directed iCBT programs also show large effect sizes in the treatment of GAD (eg, Cohen *d*=2.43 [21]). Dear et al [22] found no significant differences between guided and unguided iCBT in terms of symptom reduction, completion rates, and satisfaction in the treatment of GAD. Moreover, first evidence suggests that characteristics of the guidance, such as the frequency of supportive monitoring [23], type of reminder (eg, phone, email), and the experience or training of the support person [24], do not have a significant influence on GAD symptom reduction. Nevertheless, it is important to take steps to promote adherence and minimize the typically high dropout rates of web-based, particularly self-directed, interventions [25] (eg, motivational content).

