### Measures

Table 1 provides an overview of survey instruments at each time point, and more detailed descriptions are also provided below.

**Table 1 table1:** Survey instruments at each time point.

Time point	Survey instrument
Pretreatment measurement (T1)	Video interview: Diagnostic Interview in Mental Disorders–Open Access (DIPS-OA). Primary outcomes (self-assessed via web-based questionnaire) Generalized anxiety disorder symptomatology (Generalized Anxiety Disorder–7; GAD-7) Quality of life (World Health Organization–Five Well-Being Test; WHO-5) Secondary outcomes (self-assessed via web-based questionnaire) Coping with difficulties in everyday life due to illness (Work and Social Adjustment Scale; WSAS) Work Capability (Institute for Medical Technology Assessment Productivity Cost Questionnaire; iPCQ) Health Literacy (Mental Health Literacy Scale; MHLS). Reduction of therapy-related expenses and burdens for patients and their relatives (Client Sociodemographic and Service Receipt Inventory; CSSRI) Secondary outcomes Demographic questionnaire Anxiety symptomatology (Beck Anxiety Inventory; BAI) Depressive symptoms (Patient Health Questionnaire–9; PHQ-9)
Intermediate measurement 6 weeks after T1 (T2)	Same as T1, except that there is no video interview Further surveys Negative effects (Negative Effects Questionnaire; NEQ) Short demographic questionnaire
Posttreatment measurement 12 weeks after T1 (T3)	Same as T2

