### Additional Outcomes

The Penn State Worry Questionnaire (PSWQ [36]) is used to assess worry as an accompanying syndrome of GAD; it consists of 16 items rated on a 5-point Likert scale. The PSWQ shows internal consistencies approximately in the range between α=.84 [37] and α=.86 [38] in GAD patients.

The Beck Anxiety Inventory (BAI [39]) is used to assess the severity of anxiety in adults and adolescents. It consists of 21 descriptive statements rated on a 4-point scale. The internal consistency of the BAI is α=.90 in clinical samples. The German version was validated by Margraf and Ehlers [40].

The Patient Health Questionnaire-9 (PHQ-9 [41]) is used to assess the presence and severity of depressive disorders. The PHQ-9 consists of 9 items rated on a 4-point Likert scale and has an internal consistency of α=.89.

To capture possible negative effects of the intervention, the Negative Effects Questionnaire (NEQ [42]) is used, which consists of 32 items rated on a 4-point Likert scale. The NEQ has an internal consistency of α=.95.

The adherence of the intervention group is recorded via the log files of the web-based platform Selfapy. The number of modules that have been worked on is recorded.

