### Hypotheses

The main objective of this trial is to determine the efficacy of the 12-week Selfapy course for patients with GAD compared to a wait-list control group. Additional outcome data will be collected at 6 weeks. However, our confirmatory hypotheses, which will evaluate a positive health care effect, will focus on the 12-week outcomes. The following 2 hypotheses refer to our primary outcomes:

GAD symptomatology (measured with the GAD-7 [27]) will significantly decrease with the use of the Selfapy course for GAD after 12 weeks compared to a wait-list control group.Perceived quality of life (measured with the WHO-5 [28]) will significantly increase after 12 weeks of the Selfapy course for GAD compared to a wait-list control group.

The following secondary outcomes will only be analyzed if the hypotheses for the primary outcomes are confirmed. They will also be tested using Bonferroni-Holm adjustment:

Difficulties in daily life (measured with the WSAS [30]) will significantly decrease after using the Selfapy course for GAD after 12 weeks compared to a wait-list control group.Using the Selfapy course for GAD will lead to significantly better recovery of working ability (measured with the iPCQ [32]) after 12 weeks compared to a wait-list control group.Health literacy (measured with the MHLS [34]) will significantly improve with the use of the Selfapy course for GAD after 12 weeks compared to a wait-list control group.The extent of therapy-related efforts and burdens of patients and their relatives (measured with the CSSRI [35]) will be significantly reduced after using the Selfapy course for GAD compared to a wait-list control group after 12 weeks.

Our exploratory hypotheses do not address the target symptoms and are therefore not adjusted for α accumulation:

Worry symptoms (measured with the PSWQ [36]) will significantly decrease with the use of the Selfapy course for GAD after 12 weeks compared to a wait-list control group.Self-rated anxiety symptoms (measured with the BAI [39]) will significantly decrease with the use of the Selfapy course for GAD after 12 weeks compared to a wait-list control group.Self-rated depressive symptoms (measured with the PHQ-9 [41]) will significantly decrease with the use of the Selfapy course for GAD after 12 weeks compared to a wait-list control group.The Selfapy course for GAD will not lead to any side effects compared to a wait-list control group after 12 weeks (measured with the NEQ [42]).

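### Control-arm imputation is not restricted to efficacy outcomes, so for the NEQ it pulls the main harm comparison toward the predicted result of no side effects

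*Protocol article*

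**What the plan says.** All points are in the Methods of the protocol article.

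- **Scope (Statistical Analyses).** The intention-to-treat set is defined thus: "For the psychometric outcome analyses, all patients who were randomly assigned to the 2 conditions and completed the initial survey (T1) will be included".
- **Rule (same paragraph).** "Missing values in the data will be replaced by multiple imputations (multivariate imputation by chained equations with n=5 imputations) based on the control arm". No outcome is exempted. The article describes the inputs of the imputation model as "using the variables “age” and “gender” as predictors in addition to the measurement-repeated stress indicators". None of these records exposure to the course or module use.
- **Sensitivity analyses (same paragraph).** Last-observation-carried-forward (LOCF), baseline-observation-carried-forward (BOCF), jump-to-reference imputation and a completer analysis.
- **Harm measure (Additional Outcomes).** "To capture possible negative effects of the intervention, the Negative Effects Questionnaire (NEQ [42]) is used, which consists of 32 items". It is listed beside the PSWQ, BAI and PHQ-9 as a self-report scale.
- **Timing (Measures, Table 1).** The NEQ enters at T2, under "Further surveys Negative effects (Negative Effects Questionnaire; NEQ", and is repeated at T3. There is no T1 value.
- **Hypothesis (Hypotheses).** "The Selfapy course for GAD will not lead to any side effects compared to a wait-list control group after 12 weeks". It is exploratory and carries no multiplicity adjustment.

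**The concern.** Control-based imputation gives an intervention patient with a missing value a value modelled on people who had no access to the course. The estimated difference between the arms therefore moves toward zero. For GAD-7 and WHO-5 this is a cautious choice, because benefit has to show as a difference. For the NEQ the predicted result is the absence of a difference, so the same movement helps the hypothesis.

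At stake is the main harm statement of the trial. A finding of no side effects would rest partly on values borrowed from patients who could not have had side effects of the course. The distortion grows with the share of missing questionnaires.

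**Working it through.** **The plan's own figure.** The article gives no figure for the NEQ, so none is disputed. Its sample size sets the scale of the illustration. With d = 0.45, one-sided α = 0.025 and power 0.80 (Power and Sample Size), n per arm = 2 × (1.960 + 0.842)² / 0.45² = 77.5. This rounds up to 78, or 156 in total, as stated.

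**Inputs that the article does not give.** The share m of missing NEQ values is varied up to 40%. The size of any harm is also assumed; 0.45 SD borrows the efficacy effect size purely as an example. Here a non-responder is a patient with no NEQ value at T2 or T3.

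**Step 1: equal harm h in responders and non-responders.** Imputed non-responders contribute a difference of zero, so the expected estimate is (1 − m) × h + m × 0 = (1 − m)h. With h = 0.45 this is 0.405, 0.36, 0.315 and 0.27 SD at m = 10%, 20%, 30% and 40%. A simulation agrees (2,000 runs, 78 per arm, equal missingness in both arms, 5 imputations from the observed control distribution, Rubin's rules, two-sided 5% test):

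| Missing | Control-based estimate (SD) | Harm detected | Completer estimate (SD) | Harm detected |
|---|---|---|---|---|
| 0% | 0.45 | 0.82 | 0.45 | 0.81 |
| 10% | 0.40 | 0.66 | 0.44 | 0.74 |
| 20% | 0.35 | 0.48 | 0.45 | 0.70 |
| 30% | 0.32 | 0.35 | 0.45 | 0.66 |
| 40% | 0.26 | 0.17 | 0.44 | 0.55 |

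The completer analysis keeps the full difference here and loses only precision.

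**Step 2: more harm in non-responders.** Assume 0.3 SD in responders (h_r) and 0.8 SD in non-responders (h_n). The true difference is (1 − m)h_r + m·h_n, and the control-based estimate is (1 − m)h_r.

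- m = 20%: true 0.40, control-based 0.24, completer 0.30.
- m = 30%: true 0.45, control-based 0.21, completer 0.30.
- m = 40%: true 0.50, control-based 0.18, completer 0.30.

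If only non-responders are harmed (h_r = 0), both estimates are about zero at every m.

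**Step 3: the same on a risk scale.** Assume that a negative effect occurs in 10% of intervention responders, 30% of intervention non-responders and 5% of controls. The article defines no such binary endpoint. True excess = (1 − m) × 10% + m × 30% − 5%, which is 9, 11 and 13 points at m = 20%, 30% and 40%. Control-based excess = (1 − m) × 10% + m × 5% − 5%, which is 4, 3.5 and 3 points. The completer excess is 10% − 5% = 5 points throughout.

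**Step 4: patients with a T2 value but no T3 value.** If the T2 NEQ is among the repeated-measure predictors, the imputed T3 value is the control mean at T3 plus β × (own T2 value − control mean at T2). Here β is the slope estimated in controls. With harm h at both visits, such a patient retains βh and loses (1 − β)h. For β between 0 and 1 the pull is partial. The article does not give β, nor does it say whether the NEQ is among the predictors.

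**Step 5: the planned sensitivity analyses.**

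- Jump-to-reference draws from the control arm and so shares the direction.
- BOCF cannot be computed, because the NEQ has no T1 value.
- LOCF carries an observed T2 report forward and avoids the control-arm pull, but it needs a T2 value.
- The completer analysis avoids the pull, but it misses harm concentrated in non-responders (Steps 2 and 3).

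**The case against.** The strongest reply is that the paragraph was not written with the NEQ in mind. The NEQ is not named there. BOCF presupposes a baseline. The mixed model that follows is described for the primary and secondary confirmatory outcomes only. An article may leave the handling of an exploratory tolerability scale to a fuller document. This lowers confidence but does not remove the point. The rule is stated generally for the psychometric outcomes, the NEQ is one of them, and an analyst who follows the text would apply it.

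Stronger readings are tempting, and the documents do not support them:

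- **That every intervention patient with a missing T3 value is scored as if never exposed.** This is exact only for patients with no NEQ data. The plan uses all available data and repeated measures as predictors, so a T2 report may survive in part.
- **That no planned sensitivity analysis helps.** Two of the four avoid the control-arm pull, and the completer analysis recovers the full difference when non-responders resemble responders.
- **That dropout makes 20% to 40% missing NEQ data likely.** The Background speaks of the need to "minimize the typically high dropout rates of web-based, particularly self-directed, interventions", which concerns web-based programs in general. A patient who stops the modules can still answer the questionnaires, and then nothing is imputed. The article gives no rate of missing questionnaires.
- **That patient safety depends on this analysis.** A psychologist monitors progress and responds to adverse events (Study Design), and suicidality is asked about at all three time points (Ethical Considerations).

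**Conclusion.** The point holds with moderate confidence. As written, the main analysis of the NEQ is biased toward the result that the hypothesis predicts. The bias is complete for intervention patients without any NEQ data and at most partial for those with a T2 value. With equal harm in responders and non-responders, the difference shrinks by about the missing fraction. With more harm in non-responders, it shrinks further. The sizes shown rest on assumed missing shares and assumed harm, so they illustrate the mechanism and do not forecast this trial.

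The completer and LOCF analyses limit the damage, but they are only sensitivity analyses, and harm that is never reported stays invisible to both. The hypothesis is exploratory and the efficacy conclusions are unaffected. The change should be made, but the point does not undermine the trial.

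**What to change.** State that control-based imputation applies to efficacy outcomes only. For the NEQ:

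1. Make the main analysis as observed, by arm, using any report at T2 or T3. A patient who answered at T2 and is missing at T3 then still counts. The wording of the hypothesis should change from at 12 weeks to by 12 weeks.
2. As sensitivity analysis, impute within the patient's own arm. Then shift the imputed intervention-arm values toward more harm over a range stated in advance (delta adjustment), and report the shift at which the conclusion changes. A range of 0 to 0.5 SD would cover the gap in Step 2 (0.8 − 0.3). At m = 30% a shift of 0.5 gives 0.3 + 0.3 × 0.5 = 0.45 SD, the true value there. Own-arm imputation without a shift would not capture harm concentrated in non-responders.
3. Do not count every intervention patient without NEQ data as harmed. That would mostly measure missingness.
4. Report the number of missing NEQ questionnaires by arm and visit.

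The cost is a few sentences and slightly more analysis. No new data are needed, which matters because the article reports that all participants had finished by May 2023. If the analysis has already been run, the added analyses should be labelled as such. The harm figure may become less favourable.

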### Power and Sample Size

The between-group effect size estimate is based on recent meta-analytic evidence for effect sizes in unguided web-based psychological interventions for anxiety disorders (Cohen *d*=0.45; see, for example, McCall et al [46]). Even though Selfapy is minimally guided, we chose this meta-analysis since the degree of guidance is not associated with the effect size [16,17]. This effect size will be used as the basis for sample size design. For the planned mixed model with 2 measurement time points with a general correlation structure [47], a directed hypothesis, a group allocation of 1:1, a power of 0.80, and an α level of .025 after Bonferroni-Holm correction, a total of 156 patients (n=78 per group) are needed. The number of cases was calculated using the R tool *longpower* [48]. For the secondary outcomes, this sample size yields a power of 1–β=.67.

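### Five imputations are too few for the confirmatory analysis: at the planned effect, changing the random seed can reverse a primary decision, and some power is lost

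*Protocol article*

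**What the plan says.** In Statistical Analyses, all randomised patients who "completed the initial survey (T1) will be included in an intention-to-treat (ITT) analysis". Missing values are filled in by "multivariate imputation by chained equations with n=5 imputations", based on the control arm. The same section continues: "The confirmatory analysis of the primary outcomes consists of calculating a mixed model with 2 measurement time points". So the five imputed data sets feed the primary test.

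Power and Sample Size sets the threshold and design: "a directed hypothesis", "a power of 0.80" and "an α level of .025 after Bonferroni-Holm correction". With d = 0.45 and 1:1 allocation this gives 156 patients. Hypotheses and Statistical Analyses both make the secondary outcomes conditional on the primary hypotheses being confirmed.

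No expected rate of missing T3 data is given. The nearest statement, in Background, is that it is important to "minimize the typically high dropout rates of web-based, particularly self-directed, interventions". The article does not tie the number of imputations to the amount of missing data and sets no limit on Monte Carlo error.

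**The concern.** Multiple imputation draws random values, so the pooled estimate, standard error and p value all depend on the seed. With few imputations that dependence is not negligible. Here it meets a pass/fail threshold at each Holm step, and the primary result also opens or closes the whole secondary family. A trial sized for 80% power at .025 will often produce p values near .025, where a small shift decides the outcome. Two runs of the same analysis on the same data could then support different conclusions about a primary hypothesis. Because the number 5 is written into the article, this is a stated choice and not a detail left to an unseen analysis plan.

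**Working it through.** **Inputs.** From the article: m = 5, 78 per arm, d = 0.45, one-sided α = .025, power 0.80. Assumed: a fraction of missing information (FMI) of 0.10, 0.20 or 0.30.

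**1. The plan's own sample size.** n per arm = 2(1.960 + 0.842)² / 0.45² = 77.5, rounded up to 78, so 156 in total. This reproduces the stated figure and confirms the one-sided .025 reading. Two-sided .025 would need 188, and one-sided .05 would need 124.

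**2. Seed-to-seed noise for one fixed data set.** With within-imputation variance W and between-imputation variance B, FMI = B/(W + B) for unlimited imputations. The pooled estimate then varies across seeds with SD √(FMI/m), in units of its standard error.

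- m = 5: √(0.10/5) = 0.14, √(0.20/5) = 0.20, √(0.30/5) = 0.24
- m = 50: 0.04, 0.06, 0.08

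The estimate of B is itself noisy, varying as χ² on m − 1 = 4 degrees of freedom divided by 4.

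**3. One example.** Take a data set whose p with unlimited imputations is .015, and FMI 0.20. Pooling uses T = W + (1 + 1/m)B with Barnard-Rubin degrees of freedom (complete-data df 154), over 200,000 seed draws.

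| m | 5th to 95th percentile of p | Seeds missing .025 |
|---|---|---|
| 5 | .006 to .047 | 28% |
| 20 | .009 to .025 | 5% |
| 50 | .011 to .021 | 0.3% |
| 100 | .012 to .019 | under 0.1% |

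**4. All trials at the planned effect, with no selection on p.** The test statistic has mean 0.45 × √(78/2) × √(1 − FMI), which is 2.67, 2.51 and 2.35. Each simulated trial is pooled twice with independent seeds.

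| Assumed FMI | Seeds disagree, m = 5 | Seeds disagree, m = 100 | Power, m = 5 | Power, m = 100 |
|---|---|---|---|---|
| 0.10 | 6% | 1% | 74% | 75% |
| 0.20 | 11% | 2% | 67% | 70% |
| 0.30 | 17% | 3% | 59% | 64% |

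Most of the fall below 80% power comes from the missing data. The share due to m = 5 is the difference between the last two columns: 1, 3 and 5 points.

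**5. Other true effects.** With no effect, seeds disagree at m = 5 in 1.0%, 1.6% and 2.1% of trials, and the rejection rate is about 2.4% at both m = 5 and m = 100. At d = 0.79, the meta-analytic figure in Background, they disagree in 0.3%, 1.0% and 3.2%.

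**6. Data sets already near the threshold.** A separate simulation used control-based imputation, 78 per arm, correlation 0.5, and only data sets with p between .01 and .05. Assumed missingness was 10/20%, 20/30% and 30/30% (control/intervention). At m = 5 the less frequent decision occurred in 22%, 29% and 31% of seeds. At m = 50 this fell to between 5% and 12%.

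**The case against.** **The plan does not forecast high missingness.** A reader might infer that it does from the Background remark on dropout. That remark concerns web-based interventions in general. Study Design defines dropout as finishing no module for four weeks, which is non-use; such a patient can still answer the T3 questionnaire, and the allowance is paid on completing the study. This objection stands: every missing rate used here is an assumption.

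**The borderline figures overstate the risk.** The 22% to 31% applies only to data sets selected for being close to the threshold. This stands too, so the unselected 6% to 17% is the main figure, and it holds only at the planned effect.

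**Validity is intact.** A reader might infer that five imputations inflate false positives. They do not: type I error is about 2.4% at either m. The loss is in reproducibility and power.

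**A seed may already be fixed.** A reader might infer that an analyst is free to choose the seed after seeing results. The example R code in Multimedia Appendix 1 is not shown and may set one, so the article does not support that charge. Still, a fixed seed makes the answer repeatable without making it less arbitrary; only more imputations do that.

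**The sensitivity analyses offer context.** The last-observation, baseline-observation and completer analyses contain no imputation randomness and would sit beside a borderline result. They make other assumptions, though, and do not stabilise the confirmatory p value.

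**Conclusion.** The point holds as a matter of precision and power, not of error control. For an assumed FMI of 0.10 to 0.30 and the planned effect, m = 5 lets the seed reverse the decision on one primary outcome in about 6% to 17% of trials, against about 1% to 3% at m = 100, and costs about 1 to 5 points of power. These figures treat a single outcome at the first Holm step and use standard imputation. The article imputes from the control arm, which changes the between-imputation variance; the control-based simulation of borderline data sets agrees in direction and rough size. A result far from the threshold would be little affected.

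**What to change.** Replace n=5 with a larger number, for example 50 to 100 and at least the percentage of incomplete cases, for every multiple-imputation analysis including jump-to-reference. Report the Monte Carlo error of the primary estimate and its p value. Confirm that the analysis code sets a seed in advance. The Results section says all participants had finished by May 2023, so document the change and its timing relative to unblinding. If results were already computed with five imputations, rerun with the larger number and report both. With 156 patients, the only cost is minutes of computing time.

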### Study Design

A 2-arm randomized controlled trial is being conducted to test the efficacy of the minimally guided web-based program Selfapy for GAD. The web-based course is defined as minimally guided as it is completed independently by the participant. However, as part of the patient safety concept, a psychologist monitors the participant’s progress to support the patient and respond to adverse events, such as suicidality. The participants can ask a psychologist questions about the program via an integrated messaging function. Figure 1 shows the schematic study design for patients in the intervention group and control group. After a structured diagnostic interview (DIPS-OA [26]) to clarify the inclusion and exclusion criteria, eligible patients will receive the first questionnaire and subsequently will be randomly assigned to the intervention group or control group. Patients in the intervention group will be able to use Selfapy immediately after randomization, while the control group will only have access to Selfapy after a waiting period of 12 weeks. Interim and final evaluations will occur 6 weeks (T2) and 12 weeks (T3) after the entry survey.

Subjects in the intervention group will have free access to the 12-week internet-based self-help treatment. Participants are advised to spend at least 15 to 20 minutes per day on the program. If no module is finished over 4 weeks, this will be counted as a dropout for an additional sensitivity analysis. Patients in the control group will not receive any treatment or support from the researchers during the first 12 weeks after the initial survey. However, they are free to seek any other assistance they desire, including pharmacological and psychological treatments. All concurrent therapies will be repeat-measured using self-reports.

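### The confirmatory interaction test compares mean change and leaves the pre-randomisation baseline free by arm; adjusting for baseline would gain precision at no cost in data

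*Protocol article*

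**What the plan says.** The Statistical Analyses section fixes the confirmatory model for both primary outcomes: a random intercept per subject and "3 fixed effects (group assignment, time, and the interaction of the 2 predictors". It adds that "The 2 measurement time points are nested within subjects". The treatment effect is the time-by-group interaction, which is also the numerator of the planned effect size. The secondary confirmatory outcomes use the same model.

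The Study Design section places the baseline before allocation: "eligible patients will receive the first questionnaire and subsequently will be randomly assigned". Randomization and Blinding says the same. On later visits, "Interim and final evaluations will occur 6 weeks (T2) and 12 weeks (T3) after the entry survey". The Hypotheses section puts the confirmatory comparison at 12 weeks, so the two modelled time points are most naturally T1 and T3. The protocol does not name them, and the example R code is in an appendix that is not shown.

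Power and Sample Size uses d=0.45, "a directed hypothesis", "a group allocation of 1:1", "a power of 0.80" and "an α level of .025 after Bonferroni-Holm correction", and arrives at 78 per arm (156 in total). It states neither a T1–T3 correlation nor SDs.

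**The concern.** With two time points and a free group main effect, the interaction is the difference between arms in mean change from T1 to T3. A change score subtracts the whole of the baseline, although baseline predicts the T3 score only in proportion to the correlation between them. Because T1 precedes randomisation, the true baseline difference between arms is zero. The model nevertheless estimates one and carries its noise into the treatment effect.

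What is at stake is precision on both primary outcomes, and on the secondary outcomes that are tested only if the primaries succeed. Chance imbalance at T1 also stays partly in the estimate. Randomisation is unstratified, and the plan tests baseline differences but specifies no adjustment for them.

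**Working it through.** **Inputs from the protocol:** d=0.45; one-sided alpha 0.025; power 0.80; 1:1 allocation; 78 per arm. **Assumed, because not stated:** rho (the T1–T3 correlation, shown as a range), equal SDs at T1 and T3, complete data, and d in units of the cross-sectional SD.

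**1. The plan's own figure.** For a two-sample comparison with SD 1:

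n per arm = 2(1.960+0.8416)²/0.45² = 2×7.849/0.2025 = 77.5, rounded up to 78. Power at 78 is 0.802. The stated size reproduces.

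**2. The interaction is a change-score test.** On one simulated complete data set (78 per arm), the random-intercept interaction was -0.3424 with test statistic -2.370. The difference in mean change was -0.3424 with t = -2.370.

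**3. Variance factors, with SD 1 at both visits.**
- Change score: 2(1-rho).
- Common baseline mean or ANCOVA: 1-rho².
- Ratio: (1-rho²)/[2(1-rho)] = (1+rho)/2, which is below 1 for every rho below 1.

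**4. Power** = Φ(0.45×√(39/vf) - 1.96), where vf is the variance factor and 39 = 78/2.

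| rho | vf, change | Power, planned | vf, adjusted | Power, adjusted | n per arm for 80%, planned → adjusted |
|---|---|---|---|---|---|
| 0.3 | 1.40 | 0.661 | 0.91 | 0.838 | 109 → 71 |
| 0.4 | 1.20 | 0.728 | 0.84 | 0.866 | 94 → 66 |
| 0.5 | 1.00 | 0.802 | 0.75 | 0.901 | 78 → 59 |
| 0.6 | 0.80 | 0.881 | 0.64 | 0.940 | 63 → 50 |
| 0.7 | 0.60 | 0.952 | 0.51 | 0.976 | 47 → 40 |
| 0.8 | 0.40 | 0.993 | 0.36 | 0.997 | 32 → 28 |

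At rho 0.5 the variance falls by 25%, equivalent to 1/0.75 = 1.33 times the patients.

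**5. If d is in change-score SD units instead.** Planned power is then 0.80 at any rho, and the adjusted variance factor is (1+rho)/2. Adjusted power is 0.936, 0.901, 0.862 and 0.842 at rho 0.3, 0.5, 0.7 and 0.8.

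**6. If the SDs differ.** Let k be the T1 SD divided by the T3 SD, with d in T3 SD units. The change-score factor is 1+k²-2k·rho, the adjusted factor stays at 1-rho², and the gap is (k-rho)². At rho 0.5:
- k=0.8: 1+0.64-0.80 = 0.84 against 0.75; power about 0.87 against 0.90.
- k=0.7: 1+0.49-0.70 = 0.79 against 0.75; power about 0.885 against 0.90.

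**7. Chance imbalance.** One standard error of the baseline difference is √(2/78) = 0.16 SD. At rho 0.5 (equal SDs), such an imbalance moves the change-score estimate by (1-0.5)×0.16 = 0.08 SD relative to the adjusted one, which is 0.08/0.45 = 18% of the planned effect.

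**8. Adding T2 to the model.** With complete data and T1–T3 rho 0.5, power is unchanged: 0.802 with a free baseline and 0.901 with a common one. The table below assumes that half of the T3 dropout occurs after T2; the ranges cover several assumed correlations with T2.

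| T3 dropout (assumed) | Free baseline, without → with T2 | Common baseline, without → with T2 |
|---|---|---|
| 20% | 0.732 → 0.736 to 0.745 | 0.827 → 0.832 to 0.841 |
| 30% | 0.686 → 0.693 to 0.707 | 0.775 → 0.783 to 0.799 |

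**The case against.** The strongest reply is that the planned test is legitimate. It is unbiased under randomisation, it is prespecified, and the sample-size section names the same mixed model. That stands: this is lost efficiency, not an error, and nothing shows the stated sample size to be wrong.

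The size of the gain also depends on quantities the protocol does not give. At rho 0.7 with equal SDs it is only about 2 points. Entry is restricted by diagnosis, so T1 scores may well vary less than T3 scores, which shrinks it further (step 6). This qualifies the magnitude but not the direction, since (k-rho)² is never negative.

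A reader might infer that the trial is underpowered whenever rho is below 0.5. That follows only if d is in cross-sectional SD units. The protocol calls it a between-group effect size, which leans that way, but the effect-size formula is missing from the text and the inputs to the power software are not given. On the change-score scale, planned power is 0.80 at any rho.

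A reader might also infer that leaving T2 out wastes substantial power. It does not. T2 adds nothing with complete data and about 0.4 to 2.4 points under the assumed dropout. The planned imputation uses the repeated measures as predictors, so it may already recover part of that.

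Finally, the protocol reports that all participants had finished by May 2023 and that a results paper was in preparation. Replacing a confirmatory model at that stage needs care, and the fix allows for it.

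**Conclusion.** The point holds as a free improvement. As written, the confirmatory test is a change-score comparison that does not use the equality of expected baselines that randomisation guarantees. Baseline adjustment is never less efficient to the accuracy of these formulas. With equal SDs it multiplies the variance by (1+rho)/2, and at rho 0.5 it takes power from 0.80 to 0.90 with the same 156 patients. The gain is larger at lower rho and small at rho 0.7 to 0.8. If d is in change-score SD units, adjusted power runs from about 0.94 to 0.84 for rho 0.3 to 0.8, against 0.80 as planned.

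The conclusion rests on reading the two time points as T1 and T3. The figures rest further on complete data and on the assumed rho and SDs. The documents do not support calling the planned analysis invalid, the sample size wrong or the omission of T2 a material loss.

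**What to change.** For both primary outcomes and the continuous secondary outcomes, define the confirmatory test as the arm difference at T3, adjusted for T1, in one of two ways:

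- a constrained longitudinal model with T1 and T3 as responses, one T1 mean common to both arms, separate T3 means by arm and an unstructured covariance; or
- ANCOVA of T3 on T1 and arm, fitted in each multiply imputed data set and pooled.

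Name the two time points explicitly. The numerator of the effect size becomes the T3 arm contrast, and its denominator should be restated for the model chosen.

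T2 may be added to the longitudinal model as an option of minor value. ANCOVA of T3 on T1 is not interchangeable with a three-visit model when T3 is missing, which is why it should be run within the imputed data.

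The cost is a few lines of analysis-plan wording and a change to the example R code, with no new data. The change and its date should be documented before unblinding. If unblinding has already taken place, keep the planned model as confirmatory and report the baseline-adjusted result as a labelled sensitivity analysis.
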